### **Study design**

The first phase of this study will be a large population-based cohort study to identify incident cases of NVAf between January 1st, 2009 and 30th of June 2019; to determine the proportions of NVAf patients who have received a prescription for OACs or no treatment; to examine predictors of OACs prescribing. Given the described study aims and objectives, this study design will allow for a longitudinal analysis of incident NVAf cases and the subsequent timing of OACs prescribing with no comparator groups.

The second phase will be a comparative cohort study that aims to compare the clinical outcomes of NVAf based on their exposure status to anticoagulation therapy. Both patient groups will be identified from phase one and further divided into comparative groups of patients who have been prescribed OACs and patients with no anticoagulation therapy. The comparison will be undertaken after controlling for factors that could influence a patient's exposure to OACs and the outcomes to be explored, more details provided in section M.

Finally, the third phase of this study will be a separate analysis of the treatment group from phase two who have experienced major bleeding events. This study design is suitable for this phase as it will allow for a longitudinal analysis of NVAf patients from the indexed bleeding events and onward to evaluate the clinical outcomes (i.e. stroke, bleeding reoccurrence and mortality) related to OACs resumption or not and the timing of restarting OACs after the bleeding event, it will also allow for post-haemorrhage assessment of stroke and bleeding risk using different risk scores, and the identification of predictors for not resuming anticoagulation therapy.

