**Outcomes:**

The primary outcomes will be the prescription of OACs either VKA or NOACs, product codes for OACs are described in (Appendix 2). Status of anticoagulation therapy will be classified as either OAC prescribed or OAC not prescribed. OAC prescription will be defined as the presence of any OACs prescription during the study period. Treatment patterns for OACs users will be evaluated for (1) continuous exposure to OACs: no treatment change until end of follow-up period, defined starting from the date of first prescription to the intended duration of that prescription, plus the duration of any overlapping and successive prescriptions of the same drug within 30 days after the expected end of a prescription. For VKAs, INR measurements if available will be treated as indicator for VKA exposure and therefore treated in the same way as prescriptions; (2) OACs discontinuation: no OACs prescription after a period of therapy without resumption of OACs; (3) OACs switch: this will include four switching categories: from antiplatelet only to OACs, from VKA to NOAC, from NOACs to VKA, and between NOACs switches. OACs not prescribed will be defined as no prescription record of an OACs at any time after NVAf diagnosis, this will also include patients prescribed lone antiplatelet therapy. Proportions of patients prescribed antiplatelets such as aspirin or other antiplatelets (i.e., clopidogrel, ticagrelor, or prasugrel) within the study period will be described for both OACs exposed and not exposed patients. Products codes of antiplatelet agents can be found in (Appendix 2).

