## 2. Phase 2 - Comparative study

**Exposures:** In this cohort, prescriptions for OAC will determine patient’s exposure status. NVAf patients identified from phase one and who have received a continuous prescription of either VKAs or NOACs within one year of NVAf diagnosis will be in the OACs “exposed group”. While “OACs unexposed” patients are individuals in phase one who haven’t received a prescription for anticoagulation therapy and remained OACs free for  $\geq 1$  year from NVAf diagnosis.

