## **Data/statistical analysis**

1. Phase 1 - NVAF cohort: Annual and crude incidence rates of NVAF cases will be calculated and expressed as person-time at risk with 95% confidence intervals (95% CI). Incidence rates will be calculated by dividing the number of new diagnosed NVAF cases each year by the total population at risk during the same year. NVAF incidence in each calendar year of the study period (2009-2018) will be stratified by age and further standardized by age and deprivation quantiles. Status of anticoagulation therapy will be classified as either OAC prescribed or OAC not prescribed. OAC prescribed patients are those who received prescriptions for OACs during the study period. Treatment patterns for OAC users will be evaluated for OACs continuation, discontinuation or switched). OACs not prescribed will be defined as no prescription record of an OACs at any time after NVAF diagnosis, this will also include patients prescribed lone antiplatelet therapy. Proportions of patients prescribed antiplatelets will be described for both OACs prescribed and not prescribed patients. Baseline demographic, and clinical characteristics, and status of cancer diagnosis across OACs prescribed and not prescribed groups will be presented as number and percentage, mean $\pm$  (SD), or median (interquartile range), as appropriate. For both groups' eligibility for OACs will be described and categorized based on stroke risk according to CHA2DS2-VASc score. Trends in OACs initiation, switching from antiplatelet only to OACs, and from VKA to NOAC will be explored for each year and further stratified by eligibility for OACs and deprivation quantiles. To identify variables independently associated with OACs prescribing multivariate logistic regression models will be used and fitted with the covariates described in section N. Similarly, in a separate analysis for patients with NVAF and previously diagnosed cancer multivariate logistic regression models will be fitted to explore variables independently associated with OACs prescribing (i.e, cancer types and metastasis status). The level of statistical significance was set at  $P < 0.05$ .

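### The Phase 1 treatment patterns have no place for a user who restarts the same anticoagulant after a gap of more than 30 days, and discontinuation depends on how long each patient is observed

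*Protocol*

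**What the plan says.** Under Exposures, outcomes and covariates, Phase 1, Outcomes, the protocol sets three patterns for OAC users:

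- **Continuous:** "continuous exposure to OACs: no treatment change until end of follow-up period". The exposure period runs over overlapping prescriptions and "successive prescriptions of the same drug within 30 days after the expected end of a prescription". For VKAs there is an extra rule: "INR measurements if available will be treated as indicator for VKA exposure and therefore treated in the same way as prescriptions".
- **Discontinued:** "no OACs prescription after a period of therapy without resumption of OACs". No minimum gap is given, and no fixed window in which resumption is looked for.
- **Switched:** four categories, "from antiplatelet only to OACs, from VKA to NOAC, from NOACs to VKA, and between NOACs switches".

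Item 1 of Data/statistical analysis repeats the scheme without adding to it: "Treatment patterns for OAC users will be evaluated for OACs continuation, discontinuation or switched". Study design gives the entry window as "incident cases of NVAf between January 1st, 2009 and 30th of June 2019". The Phase 2 exposed group is defined as patients "who have received a continuous prescription of either VKAs or NOACs within one year of NVAf diagnosis". Resumption is handled as an event in its own right only in Phase 3, after a major bleed.

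**The concern.** The continuous and discontinued rules do not meet. The first tolerates a same-drug gap of up to 30 days; the second requires that OAC treatment is never seen again. A patient with a longer gap who then restarts the same drug lies between them, and no switch category covers a same-drug restart.

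The second rule also looks forward to the end of each patient's record. A patient who dies, leaves the practice or reaches the end of the data during a gap counts as discontinued. A patient with the same gap who is observed long enough to restart does not.

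What is at stake is the treatment-pattern description, in a study whose objective includes a longitudinal view of prescribing. Interrupted users would drop out of the description or be assigned ad hoc, and the discontinuation proportion would have no fixed time to which it refers.

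**Working it through.** The protocol gives no figure for treatment patterns, so there is none to reproduce. The check applies the rules literally to one constructed history.

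**Inputs**

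- From the protocol: the 30-day link for the same drug, no treatment change for continuous use, no resumption for discontinuation, and the four switch categories.
- Assumed: a minimum gap of 30 days before discontinuation is declared, because the protocol states none.
- Constructed patient: apixaban in 28-day supplies from days 0, 28 and 56, so supply ends on day 56 + 28 = 84. The next apixaban prescription is on day 144, a gap of 144 − 84 = 60 days, with no gaps after that. The permitted link ends on day 84 + 30 = 114.

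**Result by end of follow-up**

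| Follow-up ends | Continuous | Discontinued | Switched |
|---|---|---|---|
| Day 80 or 100 | yes | no | no |
| Day 120, 140 or 143 | no | yes | no |
| Day 144, 200, 365 or 700 | no | no | no |

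The prescribing does not change between rows; only the observation time does. The last row does not depend on the assumed minimum gap. From day 144 treatment has resumed, so the patient is not discontinued whatever minimum is chosen, and the 60-day gap exceeds the 30-day link, so the patient is not continuous.

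**Where the hole does not apply**

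- A restarter who later stops for good meets the discontinuation rule (the same history with a single 28-day supply after the restart, ending at day 365, is discontinued).
- A restarter who began on an antiplatelet alone falls under the first switch category.
- A restart on a different agent can be a switch.
- A VKA user with INR records during the prescription gap can count as exposed throughout.

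**Time available to be seen restarting.** Entry runs from 1 January 2009 to 30 June 2019. If follow-up closes with that window (an assumption), it ranges from about 10.5 years to almost none.

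**Direction of the effect, with assumed inputs.** Suppose half of those who stop eventually restart, time to restart is exponential with median m days among them, and nobody stops again. The share of stoppers still labelled discontinued t days after stopping is 0.5 + 0.5 × 2^(−t/m).

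| t | m = 90 | m = 180 | m = 365 |
|---|---|---|---|
| 31 days | 0.89 | 0.94 | 0.97 |
| 365 days | 0.53 | 0.62 | 0.75 |
| 1,095 days | 0.50 | 0.51 | 0.56 |

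The label shrinks as observation lengthens, although the number who stopped is the same. These inputs do not come from the protocol; they show direction only.

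**The case against.** The strongest reply is that little depends on these patterns. The Phase 1 primary outcome is whether any OAC was prescribed, and neither it nor its logistic models use the pattern classes. Phase 1 is described as hypothesis generating. The protocol does not call the patterns exhaustive or mutually exclusive, so a patient who switches and later stops may properly be counted under both. Gap lengths and reporting times are often left to an analysis plan. All of this limits the reach of the point. It does not place the plain restart case, and the last part does not dispose of it: the protocol does not leave the definition open, but states a 30-day rule and a no-resumption rule and repeats the scheme in its analysis section.

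Three stronger readings are tempting and are not supported:

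- **That any long warfarin gap followed by warfarin is unclassified.** This holds only if no INR record bridges the gap.
- **That planned comparisons of discontinuation by year of diagnosis, or between VKA and NOAC users, are biased.** The yearly trends listed in Data/statistical analysis are initiation and two kinds of switching. No such discontinuation comparison is planned.
- **That the discontinued proportion would look the same after 1 and 9 years.** A reader could get this by assuming gaps at 0.15 per year and restarts at 0.5 per year and following only the first gap: 0.15/0.35 × (exp(−0.15t) − exp(−0.5t)) gives 10.9% at 1 year and 10.6% at 9. That leaves restarters who stop again out of the discontinued class, where the protocol's rule puts them. With repeat gaps at the same rates, 0.15/0.65 × (1 − exp(−0.65t)) gives 11.0%, 22.2% and 23.0% at 1, 5 and 9 years, so the proportion doubles. Neither rate is in the protocol.

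**Conclusion.** The point holds in a limited form. As written, an OAC user with a gap of more than 30 days who restarts the same drug and remains on it to the end of follow-up belongs to no pattern, and whether a given gap counts as discontinuation depends on how long the patient is observed. The hole follows from the definitions alone. The three-stage sequence in the constructed case also uses the assumed 30-day minimum gap.

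The effect is confined to the Phase 1 treatment-pattern description. It would reach the Phase 2 exposed group only if its requirement of continuous prescription carries the Phase 1 meaning, in which case exposure would depend on later prescribing. Selection of comparison groups/controls asks only for treatment within one year of diagnosis, so this is a possibility and not an established fault. How many patients are affected cannot be determined from the protocol, which gives no rates of interruption or restart. The change is worth making before prescription episodes are classified, but it does not threaten the primary result.

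**What to change.** In the Phase 1 Outcomes section and in item 1 of Data/statistical analysis:

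1. Define discontinuation as the first gap of more than 30 days after the expected end of supply, whatever happens later. For VKAs, require also that no INR record falls in the gap, in line with the existing rule.
2. Record re-initiation, meaning an OAC prescription after such a gap, as a separate event. Interruption and cessation without observed resumption can then both be reported.
3. Handle the move from antiplatelet alone to OAC separately from the other switches. It occurs at OAC start, so a scheme that classified each user by first event would fix these patients as switchers before they could be continuous or discontinued.
4. Report discontinuation and re-initiation at fixed times from first prescription, for example 1 and 2 years, with allowance for censoring.
5. State whether the Phase 2 requirement of continuous prescription uses the Phase 1 definition.

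The cost is wording and minor recoding of prescription episodes that have to be built anyway. The reported discontinuation proportion will be higher than under the current rule, because patients who later restart will count as having discontinued; the separate re-initiation figure makes this visible.

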**Covariates:**

- Patients' demographic information (age, gender, ethnicity, body mass index (BMI), geographic location (rural vs. urban), smoking status, alcohol consumption, Charlson comorbidity index for the severity of comorbidity (Appendix 4), electronic frailty index (eFI), and the index of multiple deprivation (IMD).
- For the sub-group of patients with NVAf and history of cancer, cancer diagnosis will be assessed at the index date of NVAf diagnosis and classified by cancer type into breast, prostate, colorectal, haematological, lung, and other types, and by cancer metastasis status.
- Drugs that affect either stroke or bleeding, or commonly interact with OACs, such as antihypertensive drugs, statins, antiarrhythmics, antidiabetic drugs, anticonvulsants, non-steroidal

anti-inflammatory drugs, corticosteroids, systemic azoles, HIV protease inhibitors and ciclosporin. (Appendix 2).

- The CHA2DS2-VASc stroke risk score that consists of 9 points, one for each of: congestive heart failure (CHF), hypertension (HTN), age  $\geq 75$  years (x 2 points), diabetes mellitus (DM), prior stroke or transient ischemic attack (TIA) or thromboembolism (x 2 points), vascular disease, age 65 to 74 years, and sex category. Information included in the CHA2DS2-VASc score will be identified using Read codes (Appendix 3 and 4), except for age and sex, to build the score and assess the risk of stroke for all included patients in the cohort. Further categorization of eligibility for OACs will be carried according to individual CHA2DS2-VASc scores; “not eligible for OAC” if CHA2DS2-VASc score = 0 in males, or 1 in females; and “OAC eligible” if CHA2DS2-VASc score  $\geq 1$  in males, or  $\geq 2$  in females.
  - Bleeding risk assessment using the HAS-BLED score which consists of 9 points, one for each of: hypertension, abnormal kidney or liver function (1 point each), stroke, history of bleeding or predisposition, labile INR, elderly ( $> 65$  years), and drugs/alcohol concomitantly (1 point each). All information included in the HAS-BLED score will be identified using Read codes (Appendix 3 and 4), except for age, to build the score and assess patients’ risk for bleeding. Labile INR will not be included since it is not recorded consistently in the CPRD and because we aim is to identify the presence of prescriptions for VKA rather than checking for patient’s adherence to VKA. Bleeding tendency or predisposition will be identified through Read codes for anaemia and gastric, duodenal, and peptic ulcers (Appendix 4). Also, since alcohol consumption is not well documented in primary care, whenever possible patients will score a point for this element if there is a Read code record of heavy or problematic drinking. The bleeding risk will be categorized according to HAS-BLED score; low risk (0-1), intermediate risk (2), and high risk ( $\geq 3$ ).
  - Bleeding risk assessment using the HEMORR2HAGES score which consists of the following variables: Hepatic/renal disease (1 point each); ethanol abuse (1 point); malignancy; age  $> 75$  y (1 point); low platelets count (1); re-bleeding risk (2 points); high blood pressure (1); anaemia (1); genetic factors (1 point); falls risk (1 point); stroke (1). All these variables will be identified using Read codes (Appendix 3 and 4), except for age, to build the score and assess patients’ risk for bleeding except for genetic factors which are not accurately captured in the CPRD.
  - Combined assessment of stroke, bleeding, and mortality risk using the GARFIELD-AF model relies on the following variables: age (in years), weight, heart rate, diastolic blood pressure, ethnicity, sex, history of bleeding, heart failure, history of stroke, diabetes, smoking status, dementia, use of antiplatelet, carotid occlusive disease, chronic kidney disease (CKD) (stages III–V) and vascular disease, in which the latter is defined as history of myocardial infarction (MI) or unstable angina, aortic or peripheral artery disease. These conditions will be identified using Read codes (Appendix 3 and 4).
- All risk assessment scores will be measured at each patient’s index date.

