**Patient level data**

HES Admitted Patient Care

ONS Death Registration Data

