### **Planned use of linked data and benefit to patients in England and Wales**

For the current study, data linkages to the Hospital Episode Statistic (HES), Office for National Statistics (ONS) death registration data and index of multiple deprivation (IMD) will be required. As the included patients for particular phases will be those eligible for data linkage, then that population will be based on English practices consented to the CPRD linkage scheme. Access to the HES and ONS Mortality data are important aims as we plan to assess the association between patients' outcomes (bleeding events, stroke, and mortality) and OACs prescribing status in NVAF patients. All outcomes will be identified over the course of follow-up through relevant Read/SNOMED codes in patients' electronic records. Stroke or bleeding events will be identified through Read/SNOMED codes in patients primary care records and through linkage to inpatient HES ICD-10 codes in case of hospitalization secondary to stroke or bleeding. ONS data will be used to ascertain specific causes of death (i.e. bleeding related, cardiovascular, or all-cause death), according to ICD-10 codes. While both practice and patient level IMD data will be used to describe OACs prescribing status in terms of level of social deprivation (IMD quintiles), and as covariates in the regression models to be tested across all three phases. By using linked database that include access to longitudinal information on diagnoses, symptoms, laboratory tests, and mortality records, we will be able to thoroughly explore and compare the different outcomes associated with prescribing OACs in NVAF patients. Such information would help to inform guidelines and optimise treatment decisions of OACs for patient with NVAF.

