## Selection of comparison groups/controls

For the second phase of this study, we aim to compare the clinical outcomes of patients with NVAf prescribed OACs and who were not prescribed OACs. This will be done by including incident cases of NVAf identified from phase one cohort from 2009 to 2019 and further divide them into two groups; cases are patients treated with OACs within one year of NVAf diagnosis and controls are those who did not receive OACs for  $\geq 1$  year after NVAf diagnosis. Many confounders will be controlled for when evaluating the effect of treatment (OACs) on the clinical outcomes of interest (i.e. stroke, bleeding, or all-cause mortality). Potential confounders are likely to include patient age, sex, and presence of hypertension, diabetes, coronary artery disease, heart failure, kidney disease, liver disease, peripheral artery disease, fall risk, history of stroke or bleeding, malignancy, anaemia, alcohol abuse, antiplatelet use or non-steroidal anti-inflammatory drugs. At first, we aim to perform propensity score matching method using a multivariable logistic regression model that contains the confounders mentioned above to estimate patient's probability to receive OACs. Matching will operate by taking each case and finds the closest propensity score match among controls, within a predetermined caliper bandwidth. However, in case if the matching method failed to achieve balance among the two patient groups or caused substantial exclusion of individuals from the main cohort, then we will consider overlap propensity score weighting. By applying overlap propensity score weighting each patient's will be weight by the probability of that patient being assigned to the opposite treatment group.

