### Outcomes:

The primary outcome is the composite of ischaemic stroke and other thromboembolic events, or the occurrence of MB events defined according to the ISTH criteria (described in detail in Section D). Secondary outcomes will include CRNMB events that did not satisfy the ISTH criteria and led to hospitalization, medical or surgical treatment, or led to discontinuation of OACs. All outcomes will be identified over the course of follow-up through the identification of corresponding Read codes in patients’ records. For bleeding events since CPRD does not state the number of transfused blood units, any need for blood transfusion along with a Read code for bleeding will be classified as a MB event. Stroke or bleeding events will be identified through Read codes in patients primary care records and through linkage to inpatient HES ICD-10 codes in case of hospitalization secondary to stroke or bleeding. ONS mortality data will be used to ascertain specific causes of death (i.e. bleeding related, cardiovascular, or all-cause death) according

ICD-10 codes. All codes relevant to these outcomes are listed in Appendix 3.

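### Baseline stroke, bleeding and comorbidity items in the four risk tools are defined from Read codes without HES, although HES is used for the same kinds of event as outcomes

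*Protocol*

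**What the plan says.** All four risk tools are defined in the Protocol under Exposures, outcomes and covariates, Phase 1, Covariates.

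- CHA2DS2-VASc: "Information included in the CHA2DS2-VASc score will be identified using Read codes (Appendix 3 and 4), except for age and sex".
- HAS-BLED: "All information included in the HAS-BLED score will be identified using Read codes (Appendix 3 and 4), except for age".
- HEMORR2HAGES: "All these variables will be identified using Read codes (Appendix 3 and 4), except for age", with genetic factors left out as not accurately captured.
- GARFIELD-AF: "These conditions will be identified using Read codes (Appendix 3 and 4".

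Between them these items cover prior stroke and thromboembolism, prior bleeding, renal, liver and vascular disease, and malignancy. HES is mentioned for none of them.

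Outcomes are treated differently. The Phase 2 Outcomes section takes stroke and bleeding from primary care codes and also "through linkage to inpatient HES ICD-10 codes in case of hospitalization secondary to stroke or bleeding". The Phase 3 Exposures section finds the index major bleed from the same two sources.

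The linkage request lists "HES Admitted Patient Care". The section on planned use of linked data assigns HES and ONS to outcomes; IMD is the only linked source it names for covariates. On who is linked it says: "As the included patients for particular phases will be those eligible for data linkage". It does not name the phases.

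The scores are Phase 2 covariates, and stroke risk and bleeding risk are adjusted for in the Phase 2 Cox models (Plan for addressing confounding). CHA2DS2-VASc and HAS-BLED enter the Phase 3 Cox models, and aim 7 compares all four tools at the index bleed. Separately, the propensity-score confounders include "history of stroke or bleeding, malignancy, anaemia, alcohol abuse", with no data source given.

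**The concern.** The same clinical event is looked for with two different nets, depending on which side of the index date it falls. An admission for a bleed that reached HES but not the practice record is an outcome if it comes after NVAF diagnosis. If it came before, the patient is classed as having no bleeding history.

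Bleeding history matters to both sides of the comparison. The Study background names earlier major bleeding on anticoagulation as a contributor to under-prescription, and the Limitations section accepts that high bleeding risk may have led to no prescription. A confounder recorded with imperfect sensitivity is only partly adjusted for.

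In Phase 3 the issue is mainly misclassification. A patient can enter because of a bleed seen only in HES, while the scores at that date have only Read-code definitions. Whether such a patient scores the bleeding-history point could then depend on practice coding, which affects the score comparison in aim 7.

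**Working it through.** **Is Read codes shorthand for Read plus HES?** Where the Protocol wants HES, it adds it expressly, as in the Phase 2 Outcomes and Phase 3 Exposures. The four score definitions carry no such addition, and the linked-data section lists no use of HES for baseline history. On its face, then, the text fixes a primary care source for the scores.

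**Does anything else in the plan recover the missing history?**

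- Multiple imputation is planned for BMI, smoking and alcohol. It cannot help here, because an absent code reads as no history and not as a missing value.
- E-values gauge how strong unmeasured confounding would have to be. They do not recover history that could be measured.
- The Limitations section names alcohol, labile INR and genetic factors as score gaps, but not diagnoses recorded only in hospital.

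**Size.** The plan gives no figure to reproduce. Every input below is an assumption.

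Let p be the true prevalence of prior bleeding in a group, s the share captured by primary care codes (no false positives), and h the hazard ratio for the outcome given prior bleeding. Among patients recorded as having no history, the share who truly have one is

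m = p(1 − s) / (1 − ps).

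If OAC has no effect, the apparent ratio in that stratum is approximately

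(1 + m_exposed(h − 1)) / (1 + m_unexposed(h − 1)).

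Worked case: h = 3, s = 0.6, p = 0.05 exposed and 0.10 unexposed.

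- m_exposed = 0.05 × 0.4 / (1 − 0.03) = 0.0206
- m_unexposed = 0.10 × 0.4 / (1 − 0.06) = 0.0426
- ratio = 1.0412 / 1.0851 = 0.960

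| Prior bleeding, unexposed v exposed (h = 3) | s = 0.4 | s = 0.6 | s = 0.8 |
|---|---|---|---|
| 10% v 5% | 0.943 | 0.960 | 0.978 |
| 15% v 5% | 0.891 | 0.920 | 0.956 |

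The range is therefore about 0.89 to 0.98.

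A second calculation averages over patients with and without recorded history, standardised to the exposed group, with s from 0.5 to 0.9:

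| True prevalence, exposed v unexposed | Outcome relative risk | A true null reads |
|---|---|---|
| 5% v 15% | 2 | 0.95 to 0.99 |
| 5% v 15% | 3 | 0.91 to 0.98 |
| 10% v 30% (steeper imbalance) | 3 | 0.84 to 0.96 |
| 15% v 10% (item commoner in the exposed) | 2 to 3 | 1.005 to 1.04 |

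With complete capture (s = 1) the ratio is 1.00 in every case.

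The last row could apply to prior stroke, which carries two CHA2DS2-VASc points and so favours prescribing, although it also scores in HAS-BLED.

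**The case against.** Several points on the other side stand.

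- A reader might infer that the strongest reasons for withholding OAC go unrecorded. The documents do not show this. The Study background calls earlier major bleeding on anticoagulation one contributing factor. It also reports low prescribing above age 85, attributed mainly to overestimated bleeding risk, and age needs no code.
- A reader might infer that the whole propensity model is built on primary care codes. The list of propensity-score confounders gives no source. The Read-code definitions are the only ones offered for stroke and bleeding history, but their use there is a reading of the text. Appendix 3, cited for the scores, is not shown and is also cited for the ICD-10 outcome codes.
- A reader might take it as stated that everyone in Phases 2 and 3 is linked. The Protocol says only that particular phases are restricted in this way. Phases 2 and 3 are the natural reading, because their outcomes need HES and ONS.
- A reader might assume a single direction of bias in favour of OAC. Across the affected items the net direction is unknown.
- The prior-bleeding figures do not carry over to Phase 3. Everyone there has an index bleed, and if that bleed counts as history the item is constant and cannot confound resumption.
- The illustration treats one item alone. Correlated adjusters (anaemia and ulcer codes, Charlson index, eFI, antiplatelet use) would absorb part of the bias. The results are also small beside the planning relative risk of 2.8 for stroke.
- The Limitations section already warns that bleeding risk cannot be fully ascertained.

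None of this removes the asymmetry, which comes from the stated score definitions and not from silence.

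**Conclusion.** The point holds in a limited form. As written, prior stroke, bleeding and the other clinical items of the four risk tools are captured less completely as baseline history than stroke and bleeding are as outcomes, and nothing else in the plan repairs this. The result is avoidable residual confounding in the Phase 2 adjustment and misclassified scores at the Phase 3 index bleed.

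The size is not known from the documents. For prior bleeding in Phase 2, with assumed prevalences of 10% or 15% v 5%, a hazard ratio of 3 and 40% to 80% capture, the error is mostly a few per cent: a null reads about 0.89 to 0.98. A steeper assumed imbalance takes it to 0.84. An item commoner in treated patients moves the estimate up to about 4% the other way.

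This is a choice worth changing because the remedy is cheap. It is not an internal contradiction, and it is not shown to overturn any comparison.

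**What to change.** In linkage-eligible patients in Phases 2 and 3, define baseline history of stroke, thromboembolism, bleeding, renal disease, liver disease, vascular disease and cancer as a primary care code or any HES APC ICD-10 code before the index date. Use that definition in the propensity score and in all four risk tools, and state the source in the section that lists the propensity-score confounders.

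For the Phase 3 scores, state one rule for whether the index bleed itself counts as bleeding history, and apply it to every patient whichever source identified the bleed. Name the phases restricted to linkage-eligible patients.

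Keep the primary-care-only version for unlinked Phase 1 patients, and repeat the Phase 2 and 3 analyses with it as a sensitivity analysis. That would also show how much history the practice records miss.

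Cost: ICD-10 lists for the items that are not outcomes (lists for stroke and bleeding are already needed for the outcomes) and a look-back query. No new data request is needed, since HES APC is already on the linkage list.
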